**Figure 2 F2:**
[figure not shown]
Measurements of hematoma and PHE using 3D slicer software package. **(A)** original image of a patient with ICH. **(B)** hematoma marked with pink. **(C)** PHE marked with blue. ICH, intracerebral hemorrhage; PHE, perihematomal edema.

#### BG Monitoring

During the first 7 days after enrollment, BG will be monitored 3 times a day. In patients with hyperglycemia, BG will be monitored at least every 2 h until BG returns to normal.

#### Post-discharge Follow-Up

A telephone follow-up after discharge is planned at 90 days after enrollment. Post-discharge follow-up will be performed by the investigators in every center who did not participate in other parts of the trial, including the randomization or treatment of the subjects. When all efforts to follow-up have been made but have failed, the patients will be recorded as lost to follow-up at the end of the case report form.

### Study Outcomes

#### Efficacy Outcomes

The primary efficacy endpoint is the percentage of unfavorable outcomes (mRS ≥3) at 90 days post-enrollment. The secondary efficacy endpoints include changes in the volume of ICH and PHE between the baseline and follow-up CT scans, and changes in the clinical scores between baseline and follow-up.

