## Abstract

**Introduction:** Brain edema after acute intracerebral hemorrhage (ICH) plays a critical role in the secondary injury of ICH and may heighten the potential for a poor outcome. This trial aims to explore the efficacy of small doses of oral glibenclamide in perihematomal edema (PHE) and the prognosis of patients with ICH.

**Methods and Analysis:** The GATE-ICH trial is a multicenter randomized, controlled, assessor-blinded trial. A total of 220 adult patients with acute primary ICH in 28 study centers in China will be randomized to the glibenclamide group (glibenclamide plus guideline-recommended ICH management) or the control group (guideline-recommended ICH management). Multivariate logistic regression will be used to analyze the relationship between the treatments and primary outcome.

**Study Outcomes:** The primary efficacy outcome is the proportion of poor functional outcomes (modified Rankin Scale ≥3) at 90 days after enrollment. The secondary efficacy outcomes include changes in the volume of ICH and PHE between the baseline and follow-up computed tomography scans as well as the clinical scores between the baseline and follow-up assessments.

**Discussion:** The GATE-ICH trial will assess the effects of small doses of oral glibenclamide in reducing the PHE after ICH and improving the 90-day prognosis of patients.

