### Study Procedures

Figure 1 presents the flow chart of the GATE-ICH trial. Based on the inclusion and exclusion criteria, the potential subjects offering informed consent will be randomized. At baseline, demographics, medical history (acute ischemic stroke, ICH, coronary events, diabetes mellitus, and hypertension), physical examination results, clinical scores (NIHSS, GCS, ICH score, Barthel index, mRS), vital signs, and head CT results will be recorded. Routine laboratory tests for patients with ICH will be conducted (routine blood tests, renal and liver function tests, serum lipid, fasting glucose, routine urine tests, electrocardiography, and head CT) on days 1, 3, and 7. Clinical scores (NIHSS, GCS, Barthel index, and mRS) on day 3 and day 7 or the day of hospital discharge will be collected. The Barthel index and mRS on day 90 will be assessed. During the entire period of hospitalization, concomitant treatments, adverse events (AEs), and serious AEs (SAEs) will be documented.

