### Statistical Considerations

Patients in our study will be analyzed according to the intention-to-treat principle. Analyses will be conducted by blinded biostatisticians. Baseline data will be analyzed using univariate analyses. Categorical variables will be presented as rates, whereas continuous variables will be expressed as median (interquartile range) or mean ± standard deviation. The primary and secondary outcomes will be compared between patients randomized to the glibenclamide group and the control group using the Chi-square test or Fisher's exact-test and the Student's *t*-test or Wilcoxon rank-sum-test. Logistic multivariate analyses will be used to adjust for potential confounding effects of different variables and estimate the adjusted odds ratios and associated 95% confidence intervals. Two-sided *p*-values < 0.05 in all tests will be considered significant. The statistical analysis will be performed with SPSS version 19.0 software (SPSS Inc., Chicago, IL, USA).

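### Secondary volume and score changes are compared without baseline adjustment: a valid comparison, but generally less precise than a baseline-adjusted analysis of values already collected

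*Protocol article*

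**What the plan says.** Under Efficacy Outcomes the protocol article states: "The secondary efficacy endpoints include changes in the volume of ICH and PHE between the baseline and follow-up CT scans". The same sentence adds "changes in the clinical scores between baseline and follow-up".

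Under Statistical Considerations, "The primary and secondary outcomes will be compared between patients randomized to the glibenclamide group and the control group" by Chi-square or Fisher's exact test and, for continuous data, by Student's t-test "or Wilcoxon rank-sum-test".

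On adjustment, that section says "Logistic multivariate analyses will be used to adjust for potential confounding effects of different variables" and that the result will be adjusted odds ratios. The Abstract ties the model to one outcome: "Multivariate logistic regression will be used to analyze the relationship between the treatments and primary outcome". No baseline-adjusted model is named for a continuous outcome.

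The baseline data exist. Under Study Procedures, "clinical scores (NIHSS, GCS, ICH score, Barthel index, mRS), vital signs, and head CT results will be recorded". Imaging Evaluations has each patient's three CT scans read blind for both hematoma and PHE volume.

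**The concern.** Reducing edema is half of the stated study objective, and PHE volume is its direct measure. Endpoint and test are both stated, and together they give an unadjusted comparison of change scores.

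Subtracting the baseline is the same as adjusting for it with a slope forced to 1. Where the true slope differs from 1, two things follow:

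- The treatment estimate has more variance than it needs.
- A chance difference between arms in baseline volume carries into the estimate.

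Eligible hematomas run from 5 to 30 mL, so baseline volumes will vary. At stake is the precision of the edema comparison and of the score comparisons, not their validity.

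**Working it through.** **Inputs from the document**

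- Pilot day-7 PHE (Determination of the Sample Size): 21.74 ± 9.70 mL on glibenclamide and 31.22 ± 10.16 mL on control. Pilot arms (Intervention Arms): 10 and 12 patients.
- Total 220, allocated 1:1, with 15% assumed for non-adherence and loss. 220 × 0.85 = 187, so about 93 per arm. The 220 was set for the primary outcome; no sample size is stated for PHE.
- Two-sided 5%, 80% power.

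**Assumptions, because the document gives no figure**

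- Correlation rho between baseline and follow-up: 0.3 to 0.9.
- Ratio k of baseline SD to follow-up SD: 1 or 0.5.
- A follow-up SD equal to the pilot pooled SD.

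**Step 1. The plan's own PHE figure.** Pooled SD = √[(9 × 9.70² + 11 × 10.16²)/20] = 9.96 mL. The difference is 31.22 − 21.74 = 9.48 mL. The two-sample test gives t = −2.22 on 20 df, p = 0.038, as printed. This pilot contrast is of day-7 volumes, not of changes.

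**Step 2. Variances.** With follow-up SD s:

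- change score: (1 + k² − 2·rho·k)·s², which is 2(1 − rho)·s² when k = 1
- ANCOVA: (1 − rho²)·s²
- ratio of ANCOVA to change when k = 1: (1 + rho)/2

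| rho | ANCOVA/change, k = 1 | ANCOVA/change, k = 0.5 |
|---|---|---|
| 0.3 | 0.65 | 0.91/0.95 = 0.96 |
| 0.5 | 0.75 | 0.75/0.75 = 1.00 |
| 0.7 | 0.85 | 0.51/0.55 = 0.93 |
| 0.9 | 0.95 | 0.19/0.35 = 0.54 |

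The gain vanishes when the true slope, rho/k, equals 1 (here rho = 0.5 with k = 0.5). It is large when the slope is far from 1 in either direction.

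**Step 3. What this means for PHE (k = 1, 93 per arm, s = 9.96 mL).** Detectable difference at 80% power = 2.80 × SD × √(2/93), where SD is the square root of the relevant variance.

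| rho | Detectable, change | Detectable, ANCOVA | Power for an assumed 4 mL: change / ANCOVA |
|---|---|---|---|
| 0.3 | 4.84 mL | 3.90 mL | 64% / 82% |
| 0.5 | 4.09 mL | 3.54 mL | 78% / 89% |
| 0.7 | 3.17 mL | 2.92 mL | 94% / 97% |
| 0.9 | 1.83 mL | 1.78 mL | both about 100% |

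At the pilot difference of 9.48 mL both methods exceed 99.9% power at every rho shown.

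**Step 4. Chance imbalance.** If the arms differ by d at baseline, the change-score estimate moves by −(1 − slope)·d. Taking a baseline SD of 9.96 mL and 93 per arm, one standard error of d is 9.96 × √(2/93) = 1.46 mL. At a slope of 0.5 the estimate moves by 0.5 × 1.46 = 0.73 mL. Baseline adjustment removes this shift.

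These formulas are for the t-test. The Wilcoxon alternative was not calculated; it too is applied without baseline covariates.

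**The case against.** The strongest reply is that nothing here is invalid. Under 1:1 randomization a t-test on change is an unbiased comparison, these are secondary endpoints, and the primary binary mRS analysis does not depend on them. All of that stands. It makes this point an improvement in precision and not the correction of a bias.

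The size can also be challenged. Equal SDs are doubtful for PHE: the Introduction says it grows by about 75% in the first 24 hours and peaks at about five to six days, so follow-up volumes may well be more spread out than baseline volumes. With k = 0.5 the gain is small at rho 0.3 to 0.7. That stands too, and a reader should not infer a general saving of 15–35% of the sample size. Those figures need both equal SDs and rho between 0.3 and 0.7.

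A reader might infer other, stronger conclusions that the document does not support:

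- *The baseline values are wasted.* They are used, with a fixed coefficient of 1.
- *The score comparisons are restricted to survivors.* No text says that deaths are dropped. A rule may stand in the full protocol or SAP, a rank test could place death worst, and no expected death rate is given from which to size the problem.
- *The baseline for mRS change is undefined.* The exclusion criterion refers to prior disability, while Study Procedures records mRS at baseline and Table 1 defines t0 as the assessment before enrollment. Change from t0 is the natural reading.

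**Conclusion.** The point holds as a precision improvement for secondary endpoints. The article fixes change from baseline as the outcome and an unadjusted two-sample test as the comparison, and its only adjusted model does not apply to continuous data. In large samples ANCOVA is never less efficient than the change score, and it removes the effect of chance baseline imbalance.

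The size is uncertain. The variance reduction runs from 35% down to 5% over rho 0.3 to 0.9 with equal SDs. With the baseline SD half the follow-up SD it is about 4%, 0%, 7% and 46% at rho 0.3, 0.5, 0.7 and 0.9. The document gives neither rho nor the baseline SD. If the pilot PHE effect is real, the choice makes no practical difference to power. That effect comes from 22 patients, so a smaller one is worth planning for. How deaths are handled on the secondary scales is something to confirm, not an established error.

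**What to change.** - State that day-3 and day-7 PHE and ICH volumes will be analysed by ANCOVA, or by a repeated-measures model over both days, with baseline PHE volume and baseline hematoma volume as covariates. Use the log scale if the volumes are skewed.
- State that follow-up NIHSS, GCS and Barthel values will each be analysed with their own baseline value as a covariate.
- Confirm that the full protocol or SAP says how deaths are handled on these scales.

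The cost is a change of analysis wording, made before the treatment codes are opened. The baseline scores and CT volumes needed are already collected. Time from onset to baseline CT could be a useful further covariate, but Study Procedures does not list it as recorded, so its availability would have to be checked. An ordinal mRS analysis or composites that rank death worst would be new estimands and are not needed to settle this point.

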#### Safety Outcomes

The safety endpoints include the BG-related safety and cardiac-related safety of glibenclamide tablets as follows: (1) hypoglycemia (BG <3.1 mmol/L), (2) symptomatic hypoglycemia (hypoglycemia with confirmed hypoglycemic symptoms), (3) incidence of cardiac AE/SAEs or a QT interval of >500 ms, and (4) incidence of all-cause mortality.

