#### Patient Safety

The study drug must be reduced to 1.25 mg twice daily if any of the following conditions are present: (1) laboratory-confirmed blood glucose (BG) level <3.1 mmol/L; (2) or three laboratory-confirmed BG levels <3.9 mmol/L within 12 h. The study drug must be discontinued if either of these conditions occur twice. In patients with hyperglycemia during their hospitalization, increasing the dosage of glibenclamide or substituting glibenclamide with other SFU agents is not permitted. In patients with a laboratory-confirmed BG level <3.9 mmol/L, administration of 50% glucose is suggested, according to the following formula: supplementation volume of 50% glucose = [100–laboratory-confirmed BG (mg/dL)] × 0.4 mL. Other highly hyperosmotic glucose solutions with the same amount of sugar are also allowed.

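### The hypoglycemia endpoints count only BG <3.1 mmol/L, so low-glucose episodes at 3.1 to <3.9 mmol/L that the protocol itself acts on stay outside the named BG-safety endpoints

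*Protocol article*

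**What the plan says.** **Endpoints (Safety Outcomes).** The BG-related safety of the tablets is assessed by two endpoints: "1) hypoglycemia (BG <3.1 mmol/L), (2) symptomatic hypoglycemia (hypoglycemia with confirmed hypoglycemic symptoms". No endpoint covers BG from 3.1 to <3.9 mmol/L, glucose given for low BG, or dose reduction or discontinuation because of low BG.

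**Actions on low glucose (Patient Safety).** The dose is reduced under either of two conditions:
- "1) laboratory-confirmed blood glucose (BG) level <3.1 mmol/L"
- "three laboratory-confirmed BG levels <3.9 mmol/L within 12 h"

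The next step is "The study drug must be discontinued if either of these conditions occur twice". Separately, "In patients with a laboratory-confirmed BG level <3.9 mmol/L, administration of 50% glucose is suggested".

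**Measurement (BG Monitoring).** "During the first 7 days after enrollment, BG will be monitored 3 times a day". This schedule is not limited to one arm.

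**The concern.** Low glucose is the harm that the protocol's own dose rules guard against. Those rules work at two levels, 3.1 and 3.9 mmol/L, while the endpoints work only at the lower one. One of the two triggers for reducing and stopping the drug therefore leaves no trace in the endpoints that are meant to describe BG-related safety.

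Two features add to this. First, symptomatic hypoglycemia is defined as "symptomatic hypoglycemia (hypoglycemia with confirmed hypoglycemic symptoms". On the natural reading, a patient with confirmed symptoms at 3.4 mmol/L is not a case. Second, glucose given at <3.9 mmol/L can stop a falling BG from reaching 3.1. The Medical Care in the Hospital section also recommends 5 or 10% glucose to avoid hypoglycemia in patients with inadequate intake, and names only the glibenclamide group. In part, the endpoint then measures what remains after rescue and prevention.

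At stake is the reading of the safety table. A low count at <3.1 mmol/L could be taken as the whole low-glucose picture even if patients were being treated or withdrawn for readings just above that cut.

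**Working it through.** The plan gives no numerical result to reproduce. The check applies the two sets of rules to the same readings.

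**Inputs**
- Endpoint event (Safety Outcomes): BG <3.1 mmol/L. The symptomatic event is the same with confirmed symptoms.
- Condition 1 (Patient Safety): one laboratory-confirmed BG <3.1 mmol/L.
- Condition 2 (Patient Safety): three laboratory-confirmed BG <3.9 mmol/L within 12 h.
- Reduction: either condition once. Discontinuation: either condition twice.
- 50% glucose suggested: any laboratory-confirmed BG <3.9 mmol/L.
- Monitoring: 3 readings a day for 7 days, so 3 × 7 = 21 scheduled readings per patient.

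**Assumptions for the examples.** Readings are taken at 07, 12 and 18 h and are all laboratory-confirmed. The article gives no clock times. From 07 to 18 h is 11 h, so one day's three readings fit inside the 12 h window and condition 2 can be met on the scheduled readings alone.

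| Readings (mmol/L) | Condition met | Action on drug | Readings at which 50% glucose is suggested | Endpoint readings (<3.1) |
|---|---|---|---|---|
| 3.4 once, with symptoms | none | none | 1 | 0 |
| 3.5, 3.4, 3.6 in one day | condition 2, once | reduced | 3 | 0 |
| 3.5, 3.4, 3.6, then 3.5, 3.3, 3.7 the next day | condition 2, twice | discontinued | 6 | 0 |
| 3.0 on each of two days | condition 1, twice | discontinued | 2 | 2 |

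The last two rows make the comparison. Both patients must come off the drug for low glucose, but only one appears in the hypoglycemia endpoints. The third row meets the same condition twice, so it leads to discontinuation whether the rule means one condition recurring or any two occurrences. Confirmed symptoms in that patient would still give zero under the symptomatic endpoint.

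**After the change.** Counting readings <3.9 mmol/L moves the third patient from 0 to 6 qualifying readings. Counting protocol-defined low-BG conditions moves the same patient from 0 to 2.

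**What cannot be computed.** The article reports no BG distribution, no hypoglycemia rate and no count of dose changes, including for the pilot study. There is no basis for a number of affected patients.

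**The case against.** **The two thresholds do not conflict.** Acting early and counting the more serious event is an ordinary design. The 3.1 mmol/L cut is used consistently: for exclusion at enrollment (Box 1), as the single-reading reduction trigger, and as the endpoint. Whether BG <3.1 mmol/L still occurs under the protocol's safeguards is a legitimate question. This stands. A reader might infer that the sections contradict each other, but they do not.

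**The episodes are not lost to the trial.** Study Procedures has concomitant treatments, AEs and SAEs documented throughout hospitalization. Monitoring includes AE/SAE reports in the monthly reports. Patient and Public Involvement has low-blood-sugar symptoms fed back by patients, assessed by investigators and confirmed, with no glucose cut-off. This stands too. A reader might infer that a patient withdrawn at 3.5 mmol/L vanishes from the safety record, and the documents do not support that. However, nothing there ensures that such an episode is classed as low glucose, and it does not enter the named endpoints.

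**The trigger is demanding.** A reader might infer that a single reading <3.9 mmol/L reduces or stops the drug. It leads only to suggested glucose. Reduction needs three within 12 h, and discontinuation needs a condition to occur twice. For a patient to be withdrawn on condition 2 alone, repeated low readings must stay within the band despite suggested glucose and a reduced dose. That is possible, but nothing shows it to be common.

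**Extra safety tables may sit in the full protocol or SAP.** This is fair for dose-change listings in general. It does not settle the point, because the article itself states both the endpoint definitions and the action thresholds, and the issue is how those stated definitions fit together. The list is introduced with a word that leaves it open, but it is then set out as specific items, so this is weak evidence that more was planned.

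**Conclusion.** The point holds as a mismatch between endpoint definition and management rule. As written, the BG-safety endpoints miss episodes at 3.1 to <3.9 mmol/L, including symptomatic ones, those given glucose, and those leading to dose reduction or discontinuation under condition 2. They can therefore understate the low-glucose burden. A first low reading already below 3.1 mmol/L is still counted, so the shortfall is confined to that band.

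Its size is unknown. It could be small, and any percentage of patients would be invented. A reader might go further and conclude that the endpoint was chosen to make the drug look safe, or that a reassuring safety result would be false. The documents support neither.

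The conclusion rests on one reading of the text: that hypoglycemia in the symptomatic endpoint carries the cut-off stated immediately before it. If the sponsor meant symptomatic episodes at any glucose level, that part falls away, but the definition should then say so. The change is worth making because it is cheap and lets the endpoints reflect both of the protocol's own triggers.

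**What to change.** Keep the <3.1 mmol/L endpoint and the symptomatic endpoint. Add to the safety outcomes, for both arms over days 1-7, the number and percentage of patients with:
1. any BG <3.9 mmol/L;
2. a symptomatic episode with BG <3.9 mmol/L;
3. glucose given for low BG, kept separate from the 5 or 10% glucose recommended for inadequate intake in the glibenclamide group.

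In the glibenclamide arm, also report dose reductions and discontinuations made under the Patient Safety rules, split by which condition triggered them. State whether a reading needs laboratory confirmation to count, since the dose rules require it and the endpoint definition does not mention it. Because treatment is open-label, item 3 should be read with the BG readings beside it.

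The cost is some endpoint wording and a few table rows. BG readings, concomitant treatments and AEs are already planned for collection. No dose, rescue or stopping rule changes, and the 3.9 mmol/L level is the protocol's own. The one downside is that the reported low-glucose figure for glibenclamide may look less favourable.

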### Blinding

The outcome assessors and data analysts will be blinded to the interventions. There will be one investigator assessing the functional outcomes in every center who will be blinded to the intervention received by the participants. All of the imaging evaluations will be conducted by independent investigators blinded to the clinical variables, interventions, and functional outcomes. The analyses will be conducted by blinded biostatisticians.

### Data Quality

To narrow the gap of uniformity between the centers and ensure the quality of the study, the following guidelines will be implemented: (1) an initial meeting will be held for all of the principal investigators and research coordinators from the participating centers before the commencement of the GATE-ICH study; (2) in each research center, the principal investigator (PI) will administer the trial and the monitor the quality of the data; (3) to ensure the quality of the trial, training sessions, phase meetings, and monthly monitoring visits at every center will be required; and (4) the Quality Control and Assurance Committee will prepare monthly reports regarding the progress of the trial, including patient recruitment, randomization, protocol adherence, and completeness of the data. The informed consent forms, case report forms, reports of AE/SAE and CT data of Digital Imaging and Communications in Medicine (DICOM) will be securely stored in a locked file cabinet in a secure office. All of the digital data will be stored in a password- and firewall-protected secure computer. The sponsor of the trial will have access to the final data.

